**Methods and analysis:**

CPAP IMPACT is a randomised clinical trial comparing bCPAP to low-flow oxygen in the treatment of severe pneumonia among high-risk children 1–59 months of age. High-risk children are stratified into two subgroups: (1) HIV infection or exposure and/or severe malnutrition; (2) severe hypoxaemia. The trial is being conducted in a Malawi district hospital and will enrol 900 participants. The primary outcome is in-hospital mortality rate of children treated with standard care as compared with bCPAP.

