Our group has documented favourable severe pneumonia outcomes in Malawian children using bCPAP in case series and reports.^15–17^ A recent randomised controlled trial conducted in Bangladesh demonstrated that children with severe hypoxaemic pneumonia had decreased mortality among those treated with bCPAP compared with standard care of low-flow oxygen.^8^ While this study’s results provide critical proof of concept, its generalisability to low-resource settings with higher pneumonia case fatality rates remains unclear. For example, the study was conducted in an intensive care unit although the majority of children aged 1–59 months with severe pneumonia are treated in district hospitals that lack intensive care.^12^ Additionally, the Bangladesh study was terminated at interim analysis due to perceived efficacy which has led some to argue that the results are difficult to interpret.^18^

No studies evaluating bCPAP among African children with severe pneumonia and high-risk conditions exist to date. Children with HIV infection, HUE, severe malnutrition and/or hypoxaemia are at greater risk of pneumonia mortality than other children and are also represented disproportionally among child pneumonia deaths globally.^3 12 19–21^ Identifying bCPAP’s impact on children with these high-risk conditions is important because of their high prevalence in low-resource African settings.^3 21–23^ Further reductions in global child pneumonia mortality will require interventions that successfully target these groups.

In addition to determining bCPAP’s effectiveness in pneumonia treatment, specific implementation challenges must also be addressed. While bCPAP may be effective in certain settings like tertiary referral hospitals, wider implementation of bCPAP to the district hospital level where most children receive hospital care may have substantial challenges. For example, bCPAP devices, while not as costly as invasive methods of ventilation, are generally more expensive than traditional low-flow oxygen nasal cannula delivery. bCPAP also requires greater patient-provider ratios of clinicians with specialised training to ensure accurate, continuous pressure delivery. Identifying the subset of patients most likely to benefit from bCPAP will assist with resource allocation, particularly where bCPAP access is limited.

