#### Inclusion/exclusion criteria

Children aged 1–59 months are enrolled if their caregiver provides written informed consent, they meet WHO-defined severe pneumonia criteria (figure 1) and have one of three high-risk conditions: severe hypoxaemia, HIV infection or exposure, and/or severe malnutrition.^4^

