**Figure 5 F5:**
[figure not shown]
Projected enrolment.

Severe hypoxaemia without comorbidity subgroup: 300 (150 per arm) children with severe hypoxaemia but without HIV infection, HUE or severe malnutrition.Power analysis subgroup 1: we estimate 13% mortality for standard care and 4% for bCPAP cases.^8^
With 95% follow-up, equal allocation to the standard care and bCPAP conditions, and the hypothesised true mortality rates described, these analyses are powered at 80%.
Comorbidity subgroup: 600 children (300 per arm) with HIV infection, HUE or severe malnutrition.Power analysis subgroup 2: we estimate 15.6% mortality for standard care and 7.1% for bCPAP cases based on relative contributions by each subgroup extrapolated from observational data. The observational data reveal approximately:10% of children are infected with HIV, with assumed standard care mortality of 30% and bCPAP mortality of 14%.^7 9^
30% of children have HUE, with assumed standard care mortality of 12% and bCPAP mortality of 5%.^7^
60% of children are severely malnourished (HIV uninfected and HIV unexposed), with assumed standard care mortality of 15% and bCPAP mortality of 7%.^5^

With 95% follow-up, equal allocation to the standard care and bCPAP conditions, and the hypothesised true morality rates described, these analyses are powered at 89%. Assuming mortality of 15.6% in the standard care arm, the sample is sufficient to reject the null hypothesis with 80% probability if the mortality rate in the bCPAP arm is 8.3% or lower.

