### Statistical methodology and analysis

Logistic regression will be used in the primary and interim outcome analyses. Hospital pneumonia outcome (pneumonia cure vs died) will be the primary endpoint; study arm (bCPAP vs standard care) will be the treatment variable in primary and interim outcome analyses.

We will employ the O’Brien-Fleming stopping rule to address any inflated type II error stemming from multiple comparisons.^25^ p Values (and Z-score cut-offs) for two-sided tests used in the first interim, second interim and final analyses will be .0006 (3.438), .0151 (2.431) and .0471 (1.985), respectively.^26^

If any significant imbalance between groups on baseline covariates is present then results of logistic regression analyses controlling for these variables will also be done. If missing data do not appear to be missing completely at random, multiple imputation methods will be used to model the missinginess mechanism based on observed data and to evaluate whether the study findings vary when accounting for missinginess.

Secondary analyses will examine whether treatment effect varies by baseline patient characteristics. As with the primary analyses, hospital pneumonia cure versus died before hospital pneumonia cure will be the outcome in logistic regression with independent variables including group assignment, patient characteristic and an interaction between group assignment and patient characteristic.

Separate models will be run for each patient characteristic of interest, including primary risk category—comorbidity (HIV infection or HUE, and/or severe acute malnutrition) and severe hypoxaemia. We will also examine whether severe hypoxaemia modifies the effect of treatment for children with a comorbidity through the use of interaction terms.

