#### We are enrolling children with severe pneumonia but without comorbidity (HIV infection or exposure, and/or severe malnutrition) and severe hypoxaemia into a parallel observational substudy

As already detailed in this work, we used existing mortality evidence to define our higher risk severe pneumonia cases as children with HIV infection, HUE, severe malnutrition or severe hypoxaemia. However, there may be other at-risk groups of children not enrolled into the trial. Therefore, to better understand whether CPAP IMPACT’s enrolment criteria have captured those at greatest mortality risk, and to better understand whether there are additional key mortality risk factors in those children not included in CPAP IMPACT, we are following until hospital outcome those children with severe pneumonia but without a comorbidity or severe hypoxaemia. Children enrolled into the observational substudy are initially evaluated by our study staff and determined to be without comorbidity. Haemoglobin levels and malaria status are collected, standard WHO severe pneumonia treatment is prescribed and then the child is transferred into the care of SDH government staff. Hospital outcomes are recorded. This comprehensive study design should provide a deeper understanding of severe pneumonia cases at a Malawian district hospital while also validating whether CPAP IMPACT has appropriately targeted children at the greatest mortality risk.

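### The planned one-factor interaction models cannot attribute a difference in bCPAP effect to comorbidity rather than to severe hypoxaemia, because no child with neither factor is randomised

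*Protocol article*

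**What the plan says.** All places are in the protocol article.

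- Inclusion/exclusion criteria: children with severe pneumonia qualify if they "have one of three high-risk conditions: severe hypoxaemia, HIV infection or exposure, and/or severe malnutrition". Any one is enough.
- Discussion, on the observational substudy: children with neither factor are not randomised; "we are following until hospital outcome those children with severe pneumonia but without a comorbidity or severe hypoxaemia".
- Sample size and power: the cohort is split in two. One part is "Severe hypoxaemia without comorbidity subgroup: 300 (150 per arm) children with severe hypoxaemia but without HIV infection, HUE or severe malnutrition". The other is "Comorbidity subgroup: 600 children (300 per arm) with HIV infection, HUE or severe malnutrition", with no restriction on oxygen saturation.
- Statistical methodology and analysis: effect modification is tested by logistic regression on arm, one patient characteristic and their interaction. "Separate models will be run for each patient characteristic of interest, including primary risk category—comorbidity" and severe hypoxaemia. The next sentence adds a test of whether severe hypoxaemia modifies the treatment effect among comorbid children.
- Introduction, on why this matters: "Identifying the subset of patients most likely to benefit from bCPAP will assist with resource allocation".

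**The concern.** The eligibility rule leaves three randomised cells: hypoxaemia only, comorbidity only, and both. Comorbidity and hypoxaemia are therefore negatively associated by design. A model with one factor and its interaction with arm compares groups that differ on the other factor too.

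The planned test of hypoxaemia among comorbid children avoids this, because comorbidity is held fixed. No matching test of comorbidity among hypoxaemic children is stated. If bCPAP works mainly in hypoxaemic children, the comorbidity interaction would suggest that comorbidity weakens the effect even when it has no influence. What is at stake is the explanation of a difference between strata, in a trial meant to inform how limited bCPAP is allocated.

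**Working it through.** **The plan's own figures.** The pooled-variance normal approximation, two-sided α = 0.05 and 95% follow-up give power of 78.1% for hypoxaemia-only (142.5 per arm, 13% v 4%; stated 80%) and 89.4% for comorbidity (285 per arm, 15.6% v 7.1%; stated 89%). Both are within two points. The article gives no figure for the interaction. Its assumed mortalities imply one:

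- hypoxaemia-only OR = (0.04/0.96)/(0.13/0.87) = 0.28
- comorbidity OR = (0.071/0.929)/(0.156/0.844) = 0.41
- ratio = 0.41/0.28 ≈ 1.5

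A ratio of that size could come from comorbidity, from hypoxaemia or from both, and the one-factor model cannot say which.

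**What can be identified.** With the neither cell empty, the full arm × comorbidity × hypoxaemia model has rank 6 of 8. A model with arm, both factors and the two arm interactions has rank 6 of 6, as does a three-level category by arm. All three cell-specific effects can be estimated.

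**Size of the confounding.** Inputs from the article: comorbid control mortality 15.6%, hypoxaemia-only control mortality 13%, 300 and 150 per arm, 95% follow-up. Assumed:

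- true OR 0.40 in every hypoxaemic child and 1.0 in every other child, with no modification by comorbidity
- share h of comorbid children who are hypoxaemic = 20%, 40% or 60% (the projected-enrolment figure is not shown)
- control risk ratio k, hypoxaemic to non-hypoxaemic within comorbid children, = 1 or 2

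Steps:

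1. Control risks: p_N = 0.156/(1 − h + hk) and p_H = k·p_N.
2. Apply the cell OR to each control odds to get the treated risks t_N and t_H.
3. Pool: t = h·t_H + (1 − h)·t_N.
4. Comorbid-group OR = [t/(1 − t)]/[0.156/0.844].
5. Interaction ratio = that OR/0.40.
6. SE of the log ratio = √Σ 1/(n·p(1 − p)) over the four arm-by-stratum groups.

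Example, h = 0.4 and k = 1: t_N = 0.156; t_H = 0.0688; t = 0.4 × 0.0688 + 0.6 × 0.156 = 0.121; OR = 0.746; ratio = 1.86. Treated risk in hypoxaemia-only is 0.0564. SE = √(0.0267 + 0.0330 + 0.0620 + 0.1319) = 0.50. Then z = ln(1.86)/0.50 ≈ 1.24, and the chance of p < 0.05 is about 24%.

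| h | k | Comorbid OR | Ratio (truth 1.0) | Chance p < 0.05 | SE, comorbidity among hypoxaemic |
|---|---|---|---|---|---|
| 0.2 | 1 | 0.87 | 2.18 | 34% | 0.78 |
| 0.2 | 2 | 0.80 | 2.00 | 28% | 0.67 |
| 0.4 | 1 | 0.75 | 1.86 | 24% | 0.63 |
| 0.4 | 2 | 0.66 | 1.64 | 16% | 0.58 |
| 0.6 | 1 | 0.63 | 1.57 | 14% | 0.57 |
| 0.6 | 2 | 0.55 | 1.37 | 9% | 0.55 |

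With an OR of 0.70 in non-hypoxaemic children, the ratio is 1.19–1.59 and the chance of p < 0.05 is 6–15%.

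**Mirror case.** If the article means two yes/no factors, the hypoxaemia model has the same problem. With OR 0.40 in comorbid and 1.0 in other children, and 10–50% of comorbid children hypoxaemic, it gives a ratio of 2.19 down to 1.65 where the truth is 1.0.

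**The planned within-comorbidity test.** In the same scenarios it recovers the true ratio. Where only hypoxaemia matters, it shows OR 0.40 in comorbid hypoxaemic children and 1.0 in the other comorbid children.

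**The case against.** The strongest reply is that arm is randomised within every subset. The risk-category model gives a valid effect in hypoxaemia-only children, and the planned interaction among comorbid children gives valid effects with and without hypoxaemia. This stands. A reader might infer that the trial cannot show which subset benefits, or that comorbid hypoxaemic children would be wrongly passed over. Neither follows, since the planned analyses already estimate the effect in those children. The missing contrast is a ratio of two ORs that the plan yields.

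The wording on risk category can also mean one two-level category or two yes/no factors. A reader might infer both that the hypoxaemia model is confounded and that no estimate covers all severely hypoxaemic children. These need opposite readings: the first needs two factors, and the second needs one category. On either reading the comorbidity contrast remains confounded.

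Comparing two pre-specified strata is legitimate as description, and that stands too. The problem begins when the difference is credited to comorbidity.

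Modifier coding is often left to an analysis plan that is not shown. Here, however, the article itself fixes separate one-characteristic models.

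The abstract names the second subgroup by hypoxaemia alone ("1) HIV infection or exposure and/or severe malnutrition; (2) severe hypoxaemia"). A reader might infer a contradiction with the sample-size section, which limits it to "children with severe hypoxaemia but without HIV infection, HUE or severe malnutrition". This is abstract shorthand, and the sample-size section gives the exact definition.

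**Conclusion.** The point holds for attribution only. The separate models cannot tell modification by comorbidity from modification by hypoxaemia, and no contrast of comorbidity within hypoxaemic children is stated. The cell structure comes straight from the eligibility rules. The size does not: the spurious ratio of about 1.4–2.2 (1.2–1.6 under the milder scenario) rests on assumed odds ratios, hypoxaemic shares and control risks. The interaction is also imprecise (SE about 0.5), so a spurious result would reach significance in a minority of trials. The risk is mainly one of misreading the point estimate.

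The absence of a neither cell follows from the target population and is not an error. The primary analysis and the two subgroup comparisons are unaffected. This is a worthwhile correction to a secondary analysis.

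**What to change.** In the secondary analysis, replace the separate comorbidity and hypoxaemia models with one logistic model: arm, a three-level risk category (hypoxaemia only, comorbidity only, both) and their interaction. Report from it:

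- the bCPAP effect in each of the three cells
- the already planned hypoxaemia contrast among comorbid children
- an added comorbidity contrast among hypoxaemic children
- the effect in all severely hypoxaemic children, with or without comorbidity

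State that the difference between the two enrolment strata will not be interpreted as an effect of comorbidity.

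The cost is wording only. Oxygen saturation, HIV and nutritional status already determine eligibility, and no extra children are needed. The downside is precision. The added contrast has an SE of the log ratio of about 0.55–0.8 under the assumed shares, so its 95% interval reaches a factor of roughly 3 to 4.6 either side of the estimate. It will rarely settle the question and should be labelled exploratory.

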## Ethics and dissemination

### Ethical approval and consent

The study received approval from the Johns Hopkins Institutional Review Board and the Malawi National Health Sciences Research Committee. Written informed consent is obtained from all eligible children’s guardians prior to enrolment.

### Patient safety

Study staff are present in the hospital at all times (ie, 24 hours/day and 7 days/week). All adverse events are reported immediately to a study investigator and documented in a separate adverse event form. Death and withdrawal from the study unexpectedly are considered adverse events. The Institutional Review Boards and Data Safety and Monitoring Board (DSMB) review cumulative safety and study data after 30% enrolment and 60% enrolment and ad hoc as is necessary. The DSMB reports are shared with both the funding agency and investigators.

### Dissemination

We plan to disseminate results of CPAP IMPACT in peer-reviewed journals and international conferences, targeting those involved in the clinical care of children in low-resource settings as well as those who develop and advise on policy and protocols in those settings, especially the Malawi Ministry of Health, Acute Respiratory Infection Control Programme. We also plan to provide this data set on an open access platform at the conclusion of the trial. The trial is registered at clinicaltrials.gov (NCT02484183).

## Discussion

The following discussion outlines our efforts to manage the following two goals: (1) a pragmatic study design that allows for applicable and generalisable results to real-world, non-study settings; (2) a study that maintains the rigours of a randomised controlled trial protocol.

### Efforts towards generalisable results

#### All children with comorbidity are started on oxygen independent of SpO_2_

We chose to initiate all enrolled children with a comorbidity (HIV infection or HUE, and/or severe malnutrition), regardless of SpO_2_, on oxygen by either low flow or bCPAP for four main reasons. First, children without severe hypoxaemia but with severe pneumonia and a comorbidity still have elevated mortality, suggesting that severe hypoxaemia should not be the only indication for bCPAP in this group of children. In most resource-rich settings, the observation of an acute illness with increased work of breathing in selected higher risk children can itself be an indication for bCPAP, since the continuous positive pressure delivered can ease respiratory distress by improving lung compliance and reducing airway resistance. Second, pulse oximetry is not widely available in Malawi; severe pneumonia, in the absence of oximetry, is a clinical indication for oxygen treatment.^4^ Third, there is evidence from Malawi that children with pneumonia and moderate hypoxaemia (SpO_2 _90%–92%) have a greater risk of hospital mortality, calling into question the currently recommended Sp0_2_ threshold of <90% for oxygen initiation.^9^ Lastly, bCPAP requires 6–8 LPM flow to maintain pressure, and this flow is delivered using an oxygen concentrator. We do not expect that district hospitals will have the technology to titrate the fractional oxygen content of the delivered flow required to maintain bCPAP pressure. In addition to an oxygen concentrator and pulse oximetry, titrating fractional oxygen content of bCPAP flow would require delivery of room-air flow and a separate oxygen analyser.

#### Children enrolled in our trial are diagnosed with severe pneumonia based on clinical criteria

Given our goal is to make the trial results as generalisable as possible, we choose to use clinical diagnosis of WHO severe pneumonia alone as inclusion criteria. While chest radiographs may add improved specificity to the clinical diagnosis of severe pneumonia, the majority of low-resource settings do not have access to radiographs and are diagnosed with severe pneumonia based on WHO criteria alone.^27^

In addition, chest radiographs alone are an imperfect reference standard to diagnose pneumonia and are not routinely recommended for pneumonia diagnosis by the WHO.^4 28^ Instead, chest radiographs are recommended mainly for children who fail first-line pneumonia treatment.^4^ In the recently completed multicountry Pneumonia Etiology for Child Health study, approximately 45% of children with chest indrawing or danger signs had a normal chest radiograph ([name], personal communication).

#### We limit bCPAP pressures to 8 cmH_2_0 (children aged 2–59 months) and 7 cmH_2_0 (children aged 1–2 months)

An important risk of higher bCPAP pressures is a pneumothorax. Higher bCPAP pressures are commonly used in resource-rich settings with advanced, continuous monitoring that allows for immediate detection of a pneumothorax. In a low-resource setting, with limited monitoring, we determined *a priori* that we would limit bCPAP pressures to pressures safely used in previously reported observational studies.^16 17^ Notably, two blinded paediatric intensivists independently reviewed this protocol and agreed with this approach prior to study implementation. Future work could examine whether higher bCPAP pressures are feasible, effective and safe in routine care settings with limited supervision and safety measures.

#### We are enrolling children with severe pneumonia but without comorbidity (HIV infection or exposure, and/or severe malnutrition) and severe hypoxaemia into a parallel observational substudy

As already detailed in this work, we used existing mortality evidence to define our higher risk severe pneumonia cases as children with HIV infection, HUE, severe malnutrition or severe hypoxaemia. However, there may be other at-risk groups of children not enrolled into the trial. Therefore, to better understand whether CPAP IMPACT’s enrolment criteria have captured those at greatest mortality risk, and to better understand whether there are additional key mortality risk factors in those children not included in CPAP IMPACT, we are following until hospital outcome those children with severe pneumonia but without a comorbidity or severe hypoxaemia. Children enrolled into the observational substudy are initially evaluated by our study staff and determined to be without comorbidity. Haemoglobin levels and malaria status are collected, standard WHO severe pneumonia treatment is prescribed and then the child is transferred into the care of SDH government staff. Hospital outcomes are recorded. This comprehensive study design should provide a deeper understanding of severe pneumonia cases at a Malawian district hospital while also validating whether CPAP IMPACT has appropriately targeted children at the greatest mortality risk.

### Efforts towards rigorous protocol

#### We are using the *Fisher & Paykel Bubble CPAP* system for this study’s bCPAP device

While such a system is standard of care in most resource-rich settings, a hybrid, locally designed bCPAP system is more commonly used in low-resource settings.^15 16^ Previously we have used locally designed systems, but for this study we instead chose to use the commercially available Fisher & Paykel system.

Our previous work identified that if flow is not warmed and humidified, secretions can harden and cause nasal obstruction.^15^ The Fisher & Paykel system delivers warmed, humidified flow. In addition, we determined that, for this initial trial, using a validated commercial device would increase the precision of bCPAP pressure to the patient.

